**Figure 1 F1:**
[figure not shown]
Overall study design at the country level. SOC, standard of care; TDA, treatment decision algorithm.

**Table 1 T1:** Data collection and tools

	Site selection and formative research	Effectiveness	Acceptability	Implementation	Health economics	Health policy	Timing of data collection *Target population*	Data collected *Data collection method*
Aggregated data	X	X					Retrospective, SOC, intervention and follow-up *Children attending care, children with TB*	Aggregated health data routinely reported to the MoH in the national DHIS2 database including OPD attendance, number of children in high-risk groups, number of TB notifications in children, among others.
Individual data-based registers		X					Retrospective, SOC, intervention and follow-up *Children with presumptive TB and TB*	Data from presumptive TB registers and from TB treatment registers *Reported in created modules in DHIS2*
EMR		X					SOC in additional district only and intervention *Children with presumptive TB*	Demographics, clinical and anthropometric data, HIV status, radiological data and abdominal ultrasound examination, laboratory data, TDA used and score, TB severity assessment, TB treatment if initiated and duration, TB treatment outcomes, comorbidity management including antiretroviral treatment, nutrition therapy and status at follow-up visit *EMR data entry on tablet in DHIS2*
Child TB questionnaire	X		X	X			Formative phase and before end of trial *HCWs*	Knowledge, attitudes and practices of HCWs, their readiness to and their perceived feasibility of TDAs for childhood TB. *Self-administered REDCap questionnaire on tablet, with support from social sciences research assistants (SSRAs*).
TB diagnosis questionnaire			X	X			Quarterly (implementation and intervention) 6 monthly (acceptability) *HCWs*	Structured in three modules: (1) implementation module, to assess the scope of childhood TB diagnosis activity, barriers and facilitators and context; (2) acceptability module, to document perceptions of appropriateness of, utility of and self-confidence towards the diagnostic approach used in the facility; (3) intervention module (intervention arm only), to document the experience of the comprehensive TDA-based approach. *Self-administered REDCap questionnaire on tablet, with support from SSRAs*

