### Intervention

The intervention will be a comprehensive TDA-based approach for the screening, diagnosis and management of TB in children and use of shorter treatment for children with non-severe TB (see figure 3). All sick children will be assessed using WHO TDAs A (with CXR) or B (without CXR), according to CXR availability at the facility. In Mozambique children aged 10–14 years will be assessed using the national algorithm. CLHIV and children aged <5 years hospitalised with SAM will be evaluated using the PAANTHER and TB-Speed SAM TDAs, respectively, in facilities where CXR equipment is available. The components of each TDA include data on TB exposure history, clinical signs and symptoms, microbiological testing results with Xpert MTB/RIF Ultra (Ultra) on sputum, nasopharyngeal aspiration, gastric aspiration or stool, as well as CXR examination and urine lipoarabinomannan (LAM) test result in CLHIV in both countries and in children with SAM, sepsis or chronic kidney disease stage 3 or 4 in Zambia. Abdominal ultrasound will be performed at DH for CLHIV and children hospitalised with SAM, per PAANTHER and TB-Speed SAM TDAs. CXR will be performed at DH and at some PHCs, depending on the facility’s radiological capacity. Clinical and microbiological assessment data obtained throughout the use of TDAs, as well as test results, will be incorporated in a CDSS to help with the decision on TB treatment initiation and choice of TB treatment duration. This comprehensive TDA-based approach was adopted by consensus during national workshops held in July 2023 in each participating country and involving NTPs, scientific partners and the Decide TB consortium.

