### Endpoints

The endpoints of the different research components will be quantitative (box 1), qualitative or mixed.

Box 1Trial interdisciplinary quantitative endpoints.Effectiveness endpointsPrimary endpoint: proportion of children started on treatment for tuberculosis (TB) among sick children attending care at participant health facilities for any health complaints.Proportion of children treated for TB among those with presumptive TB, including children with microbiologically confirmed TB.Proportion of children from high-risk groups treated for TB (age <2 years, children living with HIV, children with severe acute malnutrition) among all children from high-risk group attending care and among children from high-risk groups with presumptive TB.Proportion of children with TB who are microbiologically confirmed (ie, smear or Xpert or lipoarabinomannan positive), ratio of <5 years to 5–14 years among children with TB and ratio of pulmonary TB to extrapulmonary TB.Time from presumptive TB identification to final TB treatment decision and access to TB diagnostic assessment defined as the proportion of children with presumptive TB having completed assessment with the treatment decision algorithms (TDAs) and clinical decision support systemClinical Decision Support Systems, including in high-risk groups.Concordance of the TDA result and the final TB treatment decision using the proportion of children wrongly initiated or not initiated on TB treatment defined as: (1) children not started on TB treatment despite positive score; (2) children initiated on TB treatment despite negative score.Proportion of missed TB cases and over-diagnosed TB cases (unlikely TB with a positive score) compared to a reference standard diagnosis. This will be assessed in a subset of children with full diagnostic assessment (≥1 respiratory or stool sample tested with Xpert MTB/RIF Ultra, chest X-ray (CXR) availability, clinical evaluation and follow up) at district hospital or with access to CXR.Concordance of the severity evaluation and decision for short TB treatment regimen using the proportion of (1) children with 4-month TB treatment regimen used despite severe disease as assessed by the clinical/CXR evaluation; (2) children with 6-month TB treatment regimen despite non-severe disease as assessed by the clinical/CXR evaluation.Proportion of missed severe TB cases and cases over-diagnosed as severe, compared to reference standard severity assessment by expert at low level of health care: (1) children with non-severe disease according to clinical criteria despite severe disease as evaluated by expert CXR read; (2) children with clinically assessed severe disease despite non-severe disease as evaluated by expert CXR read.Proportion of children with presumptive TB and with non-severe TB disease initiated on shorter TB treatment.TB treatment outcomes as defined per WHO (treatment success, cured, treatment completion, loss to follow-up, death, treatment failure) overall and stratified by severity and regimen duration.Deaths averted assessed through modelling.Number of adults with TB, including microbiologically confirmed TB, and proportion of all TB diagnosed that is child TB.Acceptability endpointsCo-primary endpoints: clinicians stating that in their facility they are confident in their ability to decide to initiate TB treatment in a child <5 years/in a child 5–14 years.Secondary endpoint: clinicians stating that in their facility they are confident in their ability to decide to initiate TB treatment in a child.Secondary endpoints: clinicians stating that in their facility they are not over-diagnosing children <5 years/5–14 years/all children, that is, initiating children on TB treatment when they actually do not have TB.Secondary endpoints: clinicians stating that in their facility they are supporting children <5 years/5–14 years/all children with TB to access care/medication as swiftly as they should.Feasibility and implementation endpointsCo-primary endpoint: healthcare workers (HCWs) stating that in their facility they have the adequate tools to diagnose children <5 years for TB/5–14 years for TB*.Secondary endpoint: HCWs stating that in their facility they have the adequate tools to diagnose any children (<15 years) for TB*.Secondary endpoint: clinicians stating that in the last 3 months they started a child on TB treatment.Health economics endpointsa. Cost analyses of the standard of care (SOC) and of the comprehensive TDA-based approachTotal TB care costs from the health system perspective.Unit cost per TB care activity (eg, clinical assessment, CXR).Total TB care costs of overdiagnosis (false positive)—intervention only.Total costs incurred by parents/caregivers for receiving child TB care.b. Cost-effectiveness of the comprehensive TDA-based approach compared to the SOC:Modelled health impact measure:Number of children treated for TB.Number of adults treated for TB.Number of deaths.Disability-adjusted life years (DALYs): measure of healthy life lost, either through premature death or living with disability due to illness.Cost-effectiveness measure, that is, incremental cost per:Incremental number of children treated for TB.Death averted.DALY averted.c. Budget impact of the comprehensive TDA-based approach scale-up compared to the SOC over 5 years:Cost of scaling up the comprehensive TDA-based approach nationally.Cumulative number of children and adults treated for TB, lives saved and DALYs averted during a 5-year scale-up.

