
The primary effectiveness endpoint will be the proportion of children started on TB treatment among sick children attending care at selected facilities for any health complaint, calculated during the SOC and intervention periods. Secondary effectiveness endpoints include the calculation of other proportions (eg, proportion of children treated for TB—including with TB confirmed or at high risk for TB—among all children with presumptive TB, among all children from high-risk groups attending care, etc), disaggregated by age and TB status. Time between presumptive TB identification and treatment decision and initiation will be measured. Concordance between TDA results and TB treatment decision and between severity evaluation and short treatment regimen decision will be calculated. Diagnostic accuracy (sensitivity, specificity, negative and positive predictive values) of the TDAs and severity assessment accuracy will be assessed based on a reference standard determined by an endpoint review committee taking into consideration diagnostic and follow-up data.

The acceptability of the intervention will be reported as the preferences of HCWs in delivering childhood TB diagnosis and care (comparing the intervention vs SOC), the perceived social value of the intervention for HCWs and beneficiaries and the associated health systems and socioeconomic and contextual factors influencing overall acceptability.

The feasibility/implementation endpoints will be the feasibility of delivering and implementing childhood TB diagnosis and care and specifically the intervention; the fidelity to intervention delivery plan and adherence to implementation guidelines; the adaptations in implementation over time; the contextual factors influencing implementation and the sustained delivery of the intervention 6 months post implementation.

Health economics endpoints will include total TB care costs from both health system and patient perspectives and estimated unit costs per care activity. The cost-effectiveness of the TDA-based approach will be evaluated through incremental cost per children with TB diagnosed and treated, alongside incremental costs per death and disability-adjusted life years (DALYs) averted. Additionally, a 5-year budget impact analysis will estimate national implementation costs and endpoints such as cumulative cases treated, lives saved and DALYs averted.

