### Data collection and tools

For the effectiveness component, aggregated data originally obtained from facility registers and entered in the national DHIS2 database will be extracted; individual data from registers (TB treatment and TB presumptive registers) will also be entered on specific DHIS2 modules, in addition to the EMR. For the analysis of endpoints collected at the intervention phase and the diagnostic accuracy assessment, we will use the individual patient data collected in the EMR. For the acceptability, feasibility/implementation and policy components, we will use both quantitative data (child TB questionnaire, TB diagnosis questionnaire) and qualitative data (interviews, supervision and clinical mentoring reports, field notes). The health economics component will use questionnaires. Quantitative data from the acceptability, feasibility/implementation, health economics and policy components will be entered on the electronic data capture application Research Electronic Data Capture (REDCap; https://www.project-redcap.org/). Interviews will be captured on audio-recording devices (with respondent consent) and electronically typed/transcribed. Table 1 details the data collected, tools and methods contributing to the research components and endpoints.

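### The reference standard for TDA accuracy shares Ultra, X-ray and clinical evidence with the score it judges, so accuracy is liable to incorporation bias of unknown size

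*Protocol article*

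**What the plan says.** - **What the score contains** (Intervention): "The components of each TDA include data on TB exposure history, clinical signs and symptoms, microbiological testing results with Xpert MTB/RIF Ultra (Ultra") on several specimen types, "as well as CXR examination and urine lipoarabinomannan (LAM) test result in CLHIV in both countries", with LAM extended to some further groups in Zambia.
- **What the reference is** (Endpoints): TDA accuracy is judged "based on a reference standard determined by an endpoint review committee taking into consideration diagnostic and follow-up data".
- **Who is assessed** (Box 1): missed and over-diagnosed cases are counted in children with a full assessment, meaning "≥1 respiratory or stool sample tested with Xpert MTB/RIF Ultra, chest X-ray (CXR) availability, clinical evaluation and follow up". An over-diagnosed case is a positive score in a child whom the reference calls unlikely TB.
- **Where the data come from** (Data collection and tools): for "the diagnostic accuracy assessment, we will use the individual patient data collected in the EMR". According to Table 1, that record also holds "TDA used and score, TB severity assessment, TB treatment if initiated and duration, TB treatment outcomes".
- **Where and when** (Study type/study design; Table 1): accuracy is assessed for both standard of care (SOC) and intervention in an additional, non-randomised district per country. The electronic medical record (EMR) is in use there during SOC.
- **LAM**: a separate Box 1 endpoint counts children as "microbiologically confirmed (ie, smear or Xpert or lipoarabinomannan positive"), but LAM is not listed in the full diagnostic assessment.

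**The concern.** Overlap can distort accuracy by two routes.

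1. **Shared items.** The committee weighs the same Ultra, CXR and clinical findings that generated the score. A misleading X-ray or clinical picture can push both towards TB, so their errors are correlated.
2. **Follow-up.** This is the only named reference evidence that is not itself a score item. In the intervention phase the score helps decide treatment. A score-positive child with another illness who recovers on treatment may be read as a treatment response and counted as TB rather than as over-diagnosed.

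The Introduction cites an 85% sensitivity benchmark, with Algorithm B reported at 84%. It also says that widely varying specificities raise concern about over-diagnosis, and the Discussion presents the trial as external validation of these tools. Accuracy results will feed the later economic modelling of mortality and DALYs, and Box 1 includes the cost of false-positive diagnoses. A biased reference would carry through to these outputs.

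**Working it through.** There is no accuracy figure in the article to reproduce. The stated power (0.922 and 0.981) concerns the primary detection endpoint.

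**Step 1. Overlap, side by side**

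| Evidence | Scored by the TDA | Available to the reference |
|---|---|---|
| Clinical findings | yes | yes |
| Ultra | yes | yes |
| CXR | yes, where available | yes |
| LAM | some groups | inferred only |
| Follow-up | no | yes |

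**Step 2. Illustration for Algorithm A**

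From the Introduction: sensitivity (Se) 86%, specificity (Sp) 37%. Assumed, because the article gives neither: TB prevalence 20%, and the committee wrongly calls TB in a fraction f of score-positive children without TB, with no other reference errors.

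Per 1000 children: TP = 200 × 0.86 = 172; FN = 28; FP = 800 × 0.63 = 504; TN = 296.

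- Apparent Se = (172 + 504f) / (200 + 504f)
- Apparent Sp = 296 / (800 − 504f)
- Apparent PPV = (172 + 504f) / 676

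| f | Apparent Se | Apparent Sp | PPV | Over-diagnosed share of positives (1 − PPV) |
|---|---|---|---|---|
| 0 | 86.0% | 37.0% | 25.4% | 74.6% |
| 10% | 222.4/250.4 = 88.8% | 296/749.6 = 39.5% | 222.4/676 = 32.9% | 67.1% |
| 20% | 272.8/300.8 = 90.7% | 296/699.2 = 42.3% | 272.8/676 = 40.4% | 59.6% |

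With f = 10%, apparent Se is 91.1% at an assumed prevalence of 10% and 87.2% at 40%.

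**Step 3. Does the direction always hold?**

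Suppose the same false calls are independent of the score. At f = 10%, apparent Se = (172 + 50.4) / (200 + 80) = 222.4/280 = 79.4%, which is a fall.

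With no reference false negatives, Se is raised only if a false TB call is more likely in score-positive than in score-negative children without TB by a factor above [Se/(1−Se)] × [Sp/(1−Sp)]:

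- Algorithm A: (0.86/0.14) × (0.37/0.63) = 3.6
- Algorithm B: (0.84/0.16) × (0.30/0.70) = 2.3
- PAANTHER: (0.886/0.114) × (0.612/0.388) = 12.3
- TB-Speed SAM: (0.861/0.139) × (0.809/0.191) = 26.2

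**Step 4. Over-diagnosis**

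The over-diagnosed share of score-positives is understated whenever reference false positives among them outnumber reference false negatives among them. For Algorithm A at 20% prevalence this holds unless the committee's miss rate in score-positive TB exceeds its false-call rate in score-positive non-TB by a factor of 504/172 = 2.9. This is a weaker condition than the one for sensitivity, because it does not depend on what happens in score-negative children.

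**The case against.** **Composite reference.** Without a perfect test for childhood TB, a committee reference is hard to avoid. This stands, and the fix keeps it.

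**Committee rules.** Blinding, case definitions and sensitivity analyses normally sit in a charter or analysis plan. This stands too: silence in a journal article is not the finding. The finding rests on the overlap that the article states.

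**Direction.** A reader might infer that sensitivity is inflated and over-diagnosis understated as a matter of course. The documents do not support that. Step 3 shows that sensitivity can fall, and the thresholds for PAANTHER and TB-Speed SAM are high. Follow-up can also work against the score: untreated score-negative children who worsen reveal missed TB, and treated children who do not respond can be ruled non-TB.

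**Shared Ultra item.** A reader might also infer that this item alone lifts a score past 85%. Assume 80% sensitivity in microbiology-negative TB and that every confirmed case scores positive. Overall sensitivity, c + (1 − c) × 0.80, is then 82%, 85% or 88% when the confirmed share c is 10%, 25% or 40%. That is case mix, not bias. Ultra belongs to the deployed test, and an Ultra-positive child with TB who scores positive is a true positive. Concordance of all confirmed cases is itself an assumption, since no item weights are given.

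**Follow-up is only partly score-driven.** In the SOC phase of the additional district treatment is not score-guided. In the intervention phase clinicians may depart from the score, and Box 1 measures this.

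**Conclusion.** The point holds as a liability to incorporation bias, not as a demonstrated bias. The overlap in Ultra, CXR and clinical evidence is stated, and one record holds the score, treatment and outcome. LAM in the reference is only an inference.

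The most plausible effect is understated over-diagnosis. Raised sensitivity is possible for Algorithms A and B and less assured for the other two. Under the assumptions of Step 2 the shift for Algorithm A is about 3 to 5 points in sensitivity, 2.5 to 5 points in specificity and 7.5 to 15 points in PPV. Even then about 60–67% of score-positives remain over-diagnosed, so the signal would be weakened rather than hidden. Prevalence and the committee's error rates are assumptions, and the true size cannot be derived from the article.

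This is a secondary endpoint and the change is cheap. It is worth making because the results are meant to inform policy.

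**What to change.** Keep the committee reference and the all-children result as the main accuracy analysis. Pre-specify beside it, from item-level EMR data:

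1. Sensitivity against microbiological confirmation, with the score recomputed without its Ultra and LAM points. This removes the shared microbiology; it supplements the deployed test and does not replace it.
2. Accuracy in microbiology-negative children, where the score has to rely on its other items.
3. A sensitivity analysis in which improvement on treatment alone cannot establish TB.
4. Results shown separately for SOC-phase children of the additional district, where treatment is not score-guided. The SOC section says that no CXR is performed in Mozambique, so the number with a full assessment there may be small.

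The committee should classify without the total score or the output of the clinical decision support system (CDSS), if its charter does not already require this.

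The cost is wording in the analysis plan and charter, and extra tabulation of data already planned for collection. The downside is wider intervals in the subsets and possibly less favourable accuracy figures.

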### Data collection and tools

For the effectiveness component, aggregated data originally obtained from facility registers and entered in the national DHIS2 database will be extracted; individual data from registers (TB treatment and TB presumptive registers) will also be entered on specific DHIS2 modules, in addition to the EMR. For the analysis of endpoints collected at the intervention phase and the diagnostic accuracy assessment, we will use the individual patient data collected in the EMR. For the acceptability, feasibility/implementation and policy components, we will use both quantitative data (child TB questionnaire, TB diagnosis questionnaire) and qualitative data (interviews, supervision and clinical mentoring reports, field notes). The health economics component will use questionnaires. Quantitative data from the acceptability, feasibility/implementation, health economics and policy components will be entered on the electronic data capture application Research Electronic Data Capture (REDCap; https://www.project-redcap.org/). Interviews will be captured on audio-recording devices (with respondent consent) and electronically typed/transcribed. Table 1 details the data collected, tools and methods contributing to the research components and endpoints.

### Data management and monitoring

All individual data, clinical or collected through questionnaires and interviews will be coded using numerical identification codes. Individual and aggregated data routinely collected on DHIS2 will be stored on the servers hosted by the country’s MoH. Data collected with the EMRs will be transferred from DHIS2 to the Decide TB research database and stored on a secure data repository hosted by the University of Bordeaux; this transfer will be done using RENATER’s (French national telecommunications and data network for research and education) secure file transfer system with individual authentication. The data will be pseudonymised before transfer from the NTPs. The other research data collected (eg, audio recordings, reports, qualitative field notes) will be stored on a secure data repository via a secure file transfer protocol (SFTP) at the University of Bordeaux. The research databases on DHIS2 and REDCap will be accessible by secure authentication to a restricted user’s group. The connection will be authenticated by a user ID, password and digital certificate enabling data encryption during transfer and storage to the central server. Implementation data, such as supervision and mentoring reports stored at MoH, will be anonymised and transferred on the SFTP.

Data routinely collected on DHIS2 by NTP will be monitored using the monitoring and evaluation system in place at the country level, with additional support from the in-country and international research teams. A data monitoring committee is not needed because we are in a programmatic pilot using routine data. Quality control of quantitative and qualitative research data will include checks to identify inconsistent, incomplete or inaccurate data.

